#### **10.3.3 Visit 3 (D3 ± 2 days) to Visit 13 (D26 ± 2 days)**

Medical examination and measurement of vital signs.

Measurement of erythema, Braden scale, and NRS

- ③ Performed phototherapy.
- ④ Checked medical history, medications.
- ⑤ Check for adverse events.

#### **10.3.4 Visit 14 (D29 ± 2 days)**

Medical examination and measurement of vital signs.

Measures area assessment, Braden Scale, and NRS

Performed blood tests, urinalysis, mycology tests, and biopsies.

- ④ Checked medical history, medications.
- ⑤ Check for adverse events.

#### **10.3.5 Visit 15 (D210 ± 2 days)**

Medical examination and measurement of vital signs.

Measurement of erythema, Braden scale, and NRS.

Performed mycobacterial culture and histologic examination.

### **11 Possible side effects and precautions for use**

#### **11.1 Possible side effects**

- Possible side effects include increased exudate, bacterial growth, wound bleeding, and tissue necrosis due to stimulation of the inflammatory response.
- A 2014 Cochrane review by Chen C. et al. found that photobiologic therapy can also cause side effects such as pain, microbleeds, and redness.
- If you have an adverse event, record the name of the event and the severity of the symptoms in the case log.

### **11.2 Cautions for use**

- Do not shine the light directly into your eyes. Shining the light into your own eyes, shining it into the eyes of others, looking at it through a magnifying glass, or looking at its reflection in a mirror can cause temporary impairment of your eyes, and prolonged exposure can be harmful to your eyes.
- People with light-sensitive bodies or those taking related medications may be harmed by this product, so please consult a professional before using it.
- When using this product, you must follow the instructions in the user manual.

## **12 Stop and drop criteria**

### **12.1 Stop by**

- If an adverse event, adverse reaction, etc. is observed during the course of the trial and it is deemed unreasonable to continue the trial, the principal investigator must request the IRB to stop the trial, and the trial may be stopped based on the IRB's decision.
- If the sponsor wishes to stop the clinical trial due to reasons such as the safety of the investigational medical device, the sponsor may request the Institutional Review Board to stop the clinical trial and stop the clinical trial in accordance with the decision of the Institutional Review Board.

### **12.2 Elimination Criteria**

- Record whether all subjects in the study have completed the study, and if irradiation or observation has been stopped, record the reason. For subjects in an ongoing clinical trial, the study may be discontinued in the following cases
  - Violation of inclusion and exclusion criteria
  - Use of prohibited medications during the treatment period: steroids, immunosuppressants
  - If a subject has a serious adverse event, or if the subject requests to discontinue the study due to an adverse event, or if the investigator believes that the adverse event warrants discontinuation of the study.
  - Subjects with systemic disease that was not detected by pre-study testing.

- The subject or the subject's legal representative due to unsatisfactory treatment effectiveness during the clinical trial.

If a proxy asks to stop the test

- Violation of the protocol by the investigator or subject.
- Subject withdraws consent to participate in a clinical trial
- If a subject can't be tracked
- If you're having trouble irradiating your subjects
- The development of any other condition requiring immediate medical attention that, in the opinion of the investigator, makes it inappropriate for you to proceed with the study.

### **12.3 Handling stops and dropouts**

- If a subject drops out or is withdrawn during the study, this is documented in the case record and followed up with questionnaires or phone calls for possible adverse events.
- Dropouts will be included in the statistical processing of safety and efficacy assessments unless there is good reason or evidence to exclude them, and analyses will be conducted using the Last Observation Carrying Forward (LOCF) method, which replaces missing values with the value immediately prior to the dropout.

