**14.4 Evaluation Criteria**

- Subject's complaints of adverse events that occurred during or after use of the medical device: whether there were symptoms of irritation in the hip area (burning, hives, inflammation, itching, pain, etc.)
- Medical examination: presence of skin lesions (erythema, edema, etc.) in the hip area
- Follow-up period: Follow-up will be conducted until 6 months after the end of the study.
- Mild

Evaluate the extent of the medical findings and their causal relationship to the clinical device if they do not interfere with the subject's normal daily life, cause minimal discomfort and are easily tolerated by the subject, the treatment is testimonial and complete recovery does not affect the validity of the medical device.

- Severe (moderate)

If it causes discomfort that significantly interferes with the subject's normal daily life, is reversible with continued treatment, and does not affect the validity of the investigational medical device, the degree of medical diagnosis and the causal relationship to the

investigational medical device will be evaluated.

- severe

Evaluate the validity of the medical opinion and its causal relationship to the investigational clinical device if it prevents the subject from performing normal activities of daily living, is incurable, and if the investigational clinical device affects validity.

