## **18 Research subject risks and benefits**

For mild pressure ulcers, conservative treatment is performed and includes antibiotic therapy and wound disinfection, as well as repositioning to relieve pressure. There are many wound disinfection agents available, but each has its own limitations, and there is no clinically established method of disinfection. If you decide not to participate in this study, you will receive usual conservative care, and you will be able to decline phototherapy even during the study, and you will be able to receive usual conservative care immediately afterwards. Therefore, we will strive for recovery of your condition regardless of whether you participate in the study, and we will try to minimize harm to you.

The expected side effects of the study medical device are increased exudate in the hip area, bacterial growth, wound hemorrhage, tissue necrosis, and pain, microbleeds, and redness with photobiologic therapy.

Side effects may occur. Examples of treating adverse events as soon as they occur

In the event of any injury or damage related to this study, the sponsor (LinkOptics Co., Ltd.) will be solely responsible and will compensate for the damage. However, other injury-related or disease-related expenses, such as lost wages, will not be covered.

The expected benefit of participating in this study is that the study will pay for blood tests, urine tests, radiology tests, biopsies, and bacterial identification tests related to the study while you are participating in the study. You will be responsible for any hospitalization and laboratory fees not related to the conduct of this study.

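### Sections 12.2 and 12.3 do not separate stopping irradiation from leaving the study, and nothing asks for the week-4 wound measurement in a stopped subject who still consents and can attend

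*Protocol*

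**What the plan says.** Section 12.2 asks the site to note completion for every subject and, "if irradiation or observation has been stopped, record the reason". It then gives one list, introduced by "For subjects in an ongoing clinical trial, the study may be discontinued in the following cases". The list contains:

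- grounds that concern the device or its conduct: "If you're having trouble irradiating your subjects", "Use of prohibited medications during the treatment period: steroids, immunosuppressants", and protocol violation by investigator or subject;
- grounds that may or may not end observation: adverse events, and a request to stop "due to unsatisfactory treatment effectiveness during the clinical trial";
- grounds that do end it: consent withdrawn, or the subject cannot be tracked.

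Section 12.3 covers subjects who drop out or are withdrawn. They are to be "followed up with questionnaires or phone calls for possible adverse events", and they stay in the safety and efficacy analyses, unless there is good reason to exclude them, with LOCF for missing values.

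Section 13.1 defines the primary measures at 0 and 4 weeks. The investigator measures the ulcer with a ruler at the visit and takes a standardised photograph. Section 10.3.4 schedules Visit 14 at Day 29. Section 18 tells subjects that "you will be able to decline phototherapy even during the study, and you will be able to receive usual conservative care immediately afterwards". It does not say whether wound measurement continues after that.

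**The concern.** A subject whose irradiation stops in week 2 because the device is hard to apply, or because a prohibited drug was given, can often still be examined at Day 29. Section 12.2 mentions irradiation and observation separately but attaches no different follow-up to each. The one follow-up procedure in section 12.3 cannot yield a wound size. A site that follows the text as written would contact such a subject about adverse events and leave the week-4 value to be carried forward.

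Two things are at stake. First, the carried-forward value freezes the wound at the stopping date, whereas the question is its size at 4 weeks. Second, stopping for an adverse event, poor effect or trouble irradiating could differ between a 90 mW/cm² device and a sham at 12 mW/cm² or less, and poor effect is close to the outcome itself. If stopping differs by arm, the frozen values do not cancel.

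This is a matter for the protocol. A statistical analysis plan could replace LOCF, but it could not recover a measurement that nobody was asked to take.

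**Working it through.** **Inputs from the protocol.** Minimum of 16 subjects per arm, 15% dropout, 19 per arm and 38 in total (sections 7.3.1 and 7.3.2). Basis of the dropout rate: 45 deaths among 250 patients (section 7.3.2).

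**Reproducing the plan's own figures.**
- 16 / (1 − 0.15) = 18.8, rounded up to 19 per arm, 38 in total. This agrees with the protocol.
- 45 / 250 = 18%, which the protocol lowers to 15% because it expects lower mortality in mild ulcers.

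**Expected dropouts.** 38 × 0.15 = 5.7 subjects, leaving 19 × 0.85 = 16.15 per arm against the stated minimum of 16.

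**How many week-4 values could be recovered.** The protocol does not say what share of dropouts could still attend. Call it *s*, an assumption. Recovered values = 5.7 × *s*; observed per arm = 19 × (1 − 0.15 × (1 − *s*)).

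| *s* | Recovered of 38 | Observed per arm |
|---|---|---|
| 0 | 0 | 16.2 |
| 0.25 | 1.4 | 16.9 |
| 0.50 | 2.9 | 17.6 |
| 0.75 | 4.3 | 18.3 |
| 1 | 5.7 | 19.0 |

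Because the 15% comes from deaths, *s* could be close to 0. The protocol's figures do not narrow the range.

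**What carrying forward can do (illustration, all inputs assumed).** Suppose there is no true device effect, every wound shrinks linearly by R% over 4 weeks whether or not irradiation continues, and *k* of 19 subjects in an arm stop at week *t* and are carried forward. The arm mean is R × (1 − (*k*/19) × (1 − *t*/4)).

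- 3 stops in each arm at week 2, R = 60: 60 × (1 − 3/19 × 0.5) = 55.3 in both arms. There is no spurious difference, but shrinkage is understated by 4.7 points.
- 1 against 5 stops at week 2: difference = R × 4/19 × 0.5, which is 4.2, 6.3 and 8.4 points for R = 40, 60 and 80.
- 0 against 6 stops at week 2: difference = R × 6/19 × 0.5, which is 6.3, 9.5 and 12.6 points.
- 0 against 6 stops at week 1: difference = R × 6/19 × 0.75, which is 9.5, 14.2 and 18.9 points.

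Under these assumptions, measuring the stopped subjects at Day 29 gives R in both arms and a difference of zero. The unbalanced patterns are chosen to show the mechanism and are not predictions.

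**The case against.** The strongest reply is that this is a silence and not a rule. Section 12.2 is permissive and names irradiation and observation separately. Section 12.3 does not limit follow-up to telephone contact, and a questionnaire can be completed in person. Visits 14 and 15 are not made conditional on finishing irradiation, and section 18 can be read as letting a subject decline the light without leaving the study. All of this stands: a site could keep measuring. What remains is that no passage asks it to, while the one procedure written for dropped or withdrawn subjects is about adverse events.

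Four stronger readings are tempting, and the protocol does not support them.

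- *A reader might infer that about 6 subjects, or some sizeable fraction of them, are lost but recoverable.* The 15% is based on deaths, and it is not stated as a week-4 rate.
- *A reader might infer that stopped subjects fall out of the comparison.* Section 12.3 keeps them in by LOCF. Section 10.2 has the wound assessed at each treatment visit, so a late stopper has a recent value. The issue is the quality of the value, not exclusion.
- *A reader might infer that section 12.3 contradicts section 14.4*, which lists "Medical examination: presence of skin lesions (erythema, edema, etc.) in the hip area" among the safety criteria. Section 14.4 sets criteria in general, and section 19.3 requires appropriate medical care for adverse events during and after the study. A telephone call is a poor way to judge a skin lesion, but this is a mismatch and not a contradiction.
- *A reader might infer that every adverse-event or poor-effect stop is a stop of the device alone.* In section 12.2 some of these are the subject's own request to leave. Such a subject may not agree to be measured, so the group that can be measured is smaller than the list suggests.

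It is also fair that arm-dependent stopping is only a possibility in a trial with a blinded sham.

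**Conclusion.** The point holds as a gap in data collection. Sections 12.2 and 12.3 together provide no week-4 wound measurement for a subject who stops irradiation but remains willing and able to attend, so an obtainable primary value may be replaced by a carried-forward one.

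The size is uncertain: 0 to 5.7 values among 38 subjects, with the lower end plausible given the mortality basis of the dropout rate. Any bias depends on stopping differing between arms, which the protocol neither shows nor rules out. If stopping is balanced, the illustration shows understated healing in both arms and no false difference. With 16.15 expected completers against a minimum of 16 per arm, even one or two recovered values are useful. The change is worth making because it is cheap and cannot be made good at analysis. The protocol does not show that a large loss will occur.

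**What to change.** In section 12.2, record end of irradiation separately from end of study participation, each with its date and reason. Leave every clinical ground for stopping, and the investigator's judgement on it, unchanged.

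In section 12.3, state that subjects who stop irradiation but still consent and can attend keep the scheduled Visit 14 (Day 29) wound measurement, photograph and examination, and Visit 15 where feasible. Use questionnaire or telephone contact only when a subject cannot attend. Section 18 could add a sentence saying that declining phototherapy need not end the measurements.

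The cost is a wording amendment, with its approval, and some effort to bring a few stopped subjects back. It adds no new visits or measurements.

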**38** subjects, **19 per control and experimental group, for a total of 38 subjects.**

#### **7.3.2 Rationale**

This study is an **exploratory trial** and is intended to provide a **basis for statistical validation of a confirmatory trial**. A systematic review of the effectiveness of photobiological therapy in the treatment of pressure ulcers by Francislene FCP et al. published in 2020 found that the five reviewed trials each had between 6 and 40 patients per arm, with an average of 15.8 patients per arm. We selected 16 subjects per arm as the minimum standard for this trial, with a predicted dropout rate of 15%. We will **target 19 subjects per group for the final evaluation**.

The dropout rate was **selected based on the fact that out** of 250 patients treated by a single professor ([name], Department of Plastic Surgery) over a **recent 2-year period**, 45 patients died within the study period, resulting in a mortality rate of **18%**. As the mortality rate is relatively high in patients with moderate and severe pressure ulcers, **we predicted that the mortality rate would be lower in the subjects included in this study and** set a dropout rate of 15%.

[figure not shown]

**Figure 12. Block** diagram of this study

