## 10.2 Observations and clinical test items

- **Patient consent, screening number assignment, and demographic** survey: Before entering the study, the purpose and content of the study will be explained in detail to the subject, written consent will be obtained, a screening number will be assigned in the order of receipt of written consent, and demographic information will be collected. The following information will be recorded: whether or not written consent was given and the date of consent, subject's initials, gender, date of birth, address, and contact information.
- **Determine eligibility and assign a subject identification number:** If all of the subject inclusion criteria are yes and all of the subject exclusion criteria are no, the subject is determined to be eligible and assigned a subject identification code.
- **Medical history:** A detailed investigation and recording of the subject's medical history through a questionnaire and check of past medical records during the screening visit. This includes past history of diabetes, hypertension, surgery, medications, etc.
- **Medical examination:** A medical examination is performed at each visit, and any significant findings are recorded in the Medical Examination section of the case record,

and if significant medical findings that meet the definition of an adverse event are noted after study initiation, they are recorded in the Adverse Event case record. However, undesirable medical events that occurred prior to study initiation should be recorded in addition to the current medical history section.

- **Vital signs:** Checking the subject's vital signs at each visit, including temperature, blood pressure (systolic, diastolic), and pulse rate.
- **Wound assessment:** The investigator will assess the size (width×length×depth), color, presence of necrotic tissue, discharge, odor, microvascular bleeding, and granulation tissue formation of the pressure ulcer at each treatment visit.
- **Erythema: Asymptomatic (0 points), mild (1 point), moderate (2 points), and severe (3 points).**
- **Urticaria: Rate as asymptomatic (0 points), mild (1 point), moderate (2 points), or severe (3 points).**
- **Blisters: asymptomatic (0 points), mild (1 point), moderate (2 points), and severe (3 points).**

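### Section 12.3 fixes LOCF as the only missing-data method and lets dropouts be excluded on undefined grounds; on a healing wound this can bias the week-4 comparison

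*Protocol*

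**What the plan says.** Protocol section 12.3 sets the rule for subjects who leave: "analyses will be conducted using the Last Observation Carrying Forward (LOCF) method, which replaces missing values with the value immediately prior to the dropout". The rule covers efficacy and safety alike. On who is analysed, the section says: "Dropouts will be included in the statistical processing of safety and efficacy assessments unless there is good reason or evidence to exclude them". The protocol names no other missing-data method and no sensitivity analysis, and it does not say what counts as a good reason, who decides, or when.

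Four other places bear on the rule:

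- **Endpoint.** Section 13.1 makes wound size and re-epithelialization primary, compared between arms at weeks 0 and 4.
- **Withdrawal.** Section 12.2 lists unsatisfactory effect, adverse events and serious adverse events among the grounds for discontinuation. Section 12.3 then says leavers are "followed up with questionnaires or phone calls for possible adverse events".
- **Dropout allowance.** Section 7.3.2 takes 15%, lowered from an 18% mortality figure in one practice: "45 patients died within the study period, resulting in a mortality rate of" 18%, over two years and across ulcer severities.
- **Data available.** Section 10.2 has the investigator assess items from wound size through to "granulation tissue formation of the pressure ulcer at each treatment visit". Biopsies up to week 4 are taken only at D1 and D29, and blood and urine tests only at screening and Visit 14 (D29).

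**The concern.** LOCF is harmless only if the outcome would have stayed where it was last seen. Sections 5.2 and 8 give 1-3 months for a mild ulcer to recover, so size should be falling through the four treatment weeks. A subject who leaves in week 2 is then scored with a wound larger than the week-4 value being estimated. The arm that loses more subjects, or loses them earlier, is credited with too little healing. Because poor effect and adverse events are grounds for withdrawal, dropout could differ by arm and be related to healing.

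Three further consequences follow from the text:

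- A subject who dies before D29 would be given a week-4 wound size.
- For biopsy markers and laboratory values, the last value before D29 is the baseline one. LOCF would record no change, which could hide a laboratory change in someone withdrawn for an adverse event.
- Leaving dropouts out can push the estimate the opposite way from LOCF, so an undefined exclusion clause leaves the direction of the bias open.

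The trial is meant to supply the statistical basis for a confirmatory trial (7.3.2), so a biased estimate would carry into that design.

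**Working it through.** **Plan's own figure.** Section 7.3.2: "We selected 16 subjects per arm as the minimum standard for this trial", with 15% dropout. 16 / (1 − 0.15) = 18.8, rounded up to 19 per arm, 38 in total. This reproduces. The expected loss is 19 × 0.15 = 2.85 per arm.

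**Assumptions, because the protocol gives no values.** Healing is linear and measured in percentage points of baseline size. Dropout time is uniform over the four weeks, all dropout falls before D29, and dropout is unrelated to the individual's healing unless stated. The SD is 20 or 25 points. Simulations use 19 per arm and a two-sample t-test at two-sided 5%, since the arms are independent groups (13.1 names a paired test, which is a separate matter).

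**Formula.** A dropout is on average frozen halfway, so with true week-4 healing h and dropout proportion d:

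LOCF mean healing = h × (1 − d/2)

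**No device effect, h = 60 in both arms**

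| Dropout, arm A vs arm B | LOCF means | Spurious difference | Rejection, SD 20 |
|---|---|---|---|
| 15% vs 15% | 55.5 vs 55.5 | 0 | about 5% |
| 10% vs 20% | 57.0 vs 54.0 | 3.0 | about 7% |
| 5% vs 25% | 58.5 vs 52.5 | 6.0 | about 12-13% |

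The spurious difference favours the arm with less dropout. It scales with assumed healing: at 10% vs 20% it is 1.5, 2.5 and 3.5 points for h = 30, 50 and 70. At SD 25 the rejection rates for those three are 5.4%, 5.7% and 6.7%.

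**True effect of 20 points (device 70, sham 50)**

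- 15% in both arms: 70 × 0.925 − 50 × 0.925 = 18.5
- device 10%, sham 20%: 70 × 0.95 − 50 × 0.90 = 21.5
- device 20%, sham 10%: 70 × 0.90 − 50 × 0.95 = 15.5

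**Slow healers more likely to leave** (no device effect, h = 50, SD 25, device 5%, sham 25%). LOCF gives 3.6 points in favour of the device. Leaving the dropouts out gives 3.9 points against it. At 10% vs 20% the figures are 1.8 for and 1.9 against.

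**How much dropout falls before D29.** Subjects are followed to D210. If the 15% were spread evenly over that time (an assumption), loss by D29 would be 15% × 29/210 = 2.1%, or 19 × 0.021 = 0.4 subjects per arm. The bias shrinks in proportion: 3.0 × 29/210 = 0.4 points and 6.0 × 29/210 = 0.8 points.

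**The case against.** The strongest reply is about size. The 15% rests on two-year mortality that includes worse ulcers, and the endpoint is at week 4, so the tables above may overstate early loss several-fold. This stands: no week-4 dropout rate is given, and if few subjects leave by D29 the bias is small. The 5% vs 25% split is about 1 against 5 of 19 subjects, and nothing in the protocol predicts it. A sham control with blinded subjects and investigators is there partly to prevent such imbalance. Dropouts who were healing slowly are also misjudged less by LOCF: 3.6 points rather than 5.0 at h = 50 and 5% vs 25%.

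A reader might also infer more than the text supports:

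- *Any difference in dropout biases the result.* It does not if wounds are static, or if differences in rate and timing cancel.
- *The primary outcome is lost once a subject withdraws.* Section 12.3 describes calls and questionnaires for adverse events. It does not say that nothing else is collected, and 12.2 distinguishes stopping irradiation from stopping observation.
- *Exclusions will be decided with results in hand.* Inclusion is the default and timing is not stated. Analysis-set rules may be in an SAP that is not shown. What can be said is that the clause as written, "unless there is good reason or evidence to exclude them", sets no limit.
- *The test is invalid in general.* With equal dropout and no effect, rejection stays at about 5%.

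None of this defends LOCF as the sole method. The protocol itself fixes it, and better data are already scheduled.

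**Conclusion.** The point holds as a should-fix. Section 12.3 commits the trial to LOCF for all dropout data and leaves an undefined route for excluding dropouts. Under the protocol's own expectation of healing, LOCF can bias the week-4 comparison when dropout rate or timing differs between arms, and it shrinks a true effect at equal dropout.

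If all 15% were lost before D29, a moderate imbalance (10% vs 20%) costs about 3 points and raises the false-positive rate to about 7%. If loss were spread evenly to D210, the same relative imbalance costs about 0.4 points. Healing, SD, linearity and the dropout split between arms are all assumed. With dropout timing alike in both arms, the direction of the bias follows from healing and the dropout imbalance and does not depend on the SD. A higher grade is not warranted: the trial is exploratory with 38 subjects, the likely bias is modest unless dropout is clearly unbalanced, and the repair is a change of wording before analysis.

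**What to change.** In section 12.3:

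1. **Wound size.** Replace LOCF as the primary method with a likelihood-based repeated-measures model in all randomised subjects. Use visits already scheduled (for example D8, D15, D22 and D29), with baseline as covariate, arm by visit, and the D29 contrast as the result. Choose a suitable scale, such as percent of baseline or a transformed size, because width × length × depth may be skewed or reach zero.
2. **Re-epithelialization.** Apply the same approach where it is recorded at each visit.
3. **Exclusions.** Replace the open clause with rules fixed before unblinding, or delete it.
4. **D29 measurement.** Invite subjects who stop irradiation without withdrawing consent to the existing D29 wound measurement.
5. **Deaths.** Report them by arm, and state that the model estimate does not describe wound size after death.
6. **Biopsy markers and laboratory values.** Analyse observed values and do not carry baseline forward.
7. **LOCF.** Keep it at most as a sensitivity analysis.

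The cost is protocol wording and slightly more analysis work, with no new visits and no change to the 38 subjects. The model assumes that dropout is explained by the wound sizes already observed, and the report should say so.
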